# The AID study: protocol for a randomised controlled trial of intrauterine insemination in the natural cycle compared with intracervical insemination in the natural cycle

**DOI:** 10.1136/bmjopen-2018-026065

**Published:** 2019-07-23

**Keywords:** reproductive medicine, intrauterine insemination, intracervical insemination, donor sperm

## Abstract

**Introduction:**

At present, studies comparing intrauterine insemination in the natural cycle versus intracervical insemination in the natural cycle in women undergoing artificial insemination with donor sperm are scarce.

**Methods and analysis:**

We perform a randomised controlled non-inferiority trial among five secondary and tertiary fertility clinics in the Netherlands and one tertiary fertility clinic in Belgium. Women eligible for artificial insemination with donor sperm are included. We perform six cycles of artificial insemination with donor sperm within a time horizon of 8 months comparing intrauterine insemination in the natural cycle with intracervical insemination in the natural cycle. The primary outcome is ongoing pregnancy leading to live birth conceived within eight months after randomisation. Secondary outcomes are clinical pregnancy rate, miscarriage rate, multiple pregnancy rate, pregnancy complications (preterm birth, birth weight <2500 g, pregnancy induced hypertension, (pre-) eclampsia, Hemolysis Elevated Liver enzymes Low Platelets (HELLP)), time to ongoing pregnancy, direct and indirect costs. To demonstrate the non-inferiority of intracervical insemination with a margin of 12%, we need 208 women per arm.

**Ethics and dissemination:**

The study has been approved by the Medical Ethical Committee of the Academic Medical Centre and from the Dutch Central Committee on research involving human subjects (47330-018-13). The boards of the participating hospitals approved the study. Results will be disseminated through peer-reviewed publications and presentations at international scientific meetings.

**Trial registration number:**

NTR4462

Strengths and limitations of this studyA multicentre randomised controlled design is used.We aim to give cumulative ongoing pregnancy rates, while previous studies reported clinical pregnancy rates.A limitation is that participants and researchers were not blinded.

## Introduction

Artificial insemination with donor sperm (AID) may be performed in heterosexual couples for medical reasons or to assist lesbian couples or single women to achieve pregnancy. Medical reasons for AID include obstructive and non-obstructive azoospermia, severely impaired semen quality in couples who do not wish to undergo or were not successful with intracytoplasmatic sperm injection (ICSI), severe rhesus iso-immunisation, prevention of vertical transmission of a genetic defect or prevention of transmission of HIV in couples who do not wish to undergo semen washing.^1 2^ Women can be inseminated via the intrauterine (IUI) or the intracervical (ICI) route with or without ovarian stimulation.

A systematic review, in women who started AID, reported IUI with ovarian stimulation (IUI-OS) to be more effective than ICI-OS in terms of live birth rate (OR 2.55, 95% 0.72 to 8.96, 1 RCT, n=43) and clinical pregnancy rate (OR 2.83, 95% CI 1.38 to 5.78, 2 RCTs, n=131) at the cost of a higher multiple pregnancy rate (OR 2.77, 95% CI 1.00 to 7.69, 2 RCTs, n=131). In women who started AID in the natural cycle, IUI resulted in similar live birth rates as ICI in the natural cycle (OR 3.24, 95% 0.12–87.13, 1 RCT, n=26) but in higher clinical pregnancy rates in (OR 6.18, 95% CI 1.91 to 20.03, 2 RCTs, n=76). There were no multiple pregnancies.^3^

Multiple pregnancies are associated with increased perinatal and maternal morbidity and perinatal mortality and are regarded as an adverse treatment outcome that is no longer acceptable and should be prevented.^4–6^

Therefore, the single existing guideline on AID, published by The Royal College of Obstetrics and Gynaecology, recommends six cycles of IUI in the natural cycle.^1^

In 2012, we performed a retrospective nationwide cohort study among eight sperm banks in the Netherlands on IUI and ICI in the natural cycle. We included 1843 women of whom 1163 underwent 4269 cycles of IUI in the natural cycle and 680 underwent 2345 cycles of ICI in the natural cycle. Cumulative ongoing pregnancy rates over six treatment cycles were 40.5% for IUI and 37.9% for ICI, resulting in an HR of 1.02 (95% CI 0.84 to 1.23) for IUI versus ICI.^7^

The costs for IUI have been estimated to be four times higher than ICI, mostly because of the sperm processing inherent to IUI.^8^

Since evidence that underpins the superiority of IUI in the natural cycle over ICI in the natural cycle is scarce and IUI may generate higher costs than ICI for no increase in pregnancies, we propose a multicentre trial comparing IUI and ICI in the natural cycle with a cost-effectiveness analysis alongside the trial.

## Objective

To compare the effectiveness of six cycles of IUI in the natural cycle compared with six cycles of ICI in the natural cycle with cryopreserved donor sperm within a time horizon of eight months.

## Methods and analysis

### Study design

This study is a non-blinded, multicentre, non-inferiority randomised controlled trial among five secondary and tertiary fertility clinics in the Netherlands and one tertiary fertility clinic in Belgium. Recruitment started on 3 June 2014.

We expect to complete recruitment on 1 January 2020.

### Study population

#### Inclusion criteria

We will study women between 18 and 43 years with a regular cycle, be it spontaneously or after ovulation induction and with an indication for AID.

Indications for AID are medical reasons like obstructive and non-obstructive azoospermia, severely impaired semen quality in couples who do not wish to undergo or were not successful with ICSI, severe rhesus iso-immunisation, prevention of vertical transmission of a genetic defect or prevention of transmission of HIV in couples who do not wish to undergo semen washing, In addition, lesbian couples or single women who apply for AID are eligible to participate.

#### Exclusion criteria

Women with known double-sided tubal pathology, irregular menstrual cycles, in-vitro fertilisation or IUI in their history will not be eligible.

#### Randomisation

Randomisation is performed by accessing a web-based data system that is used for randomisation in clinical trials and will be performed centrally with the use of a permuted-block-design with randomly selected block sizes that vary between two, four and six. We used a permuted block design to randomly allocate participants to a treatment and aimed to maintain balance across treatment groups. In this way, the clinician who performs the randomisation cannot predict the next randomisation to follow. Patients are randomised individually. Patients are randomly allocated to either six cycles of IUI in the natural cycle or six cycles of ICI in the natural cycle.

#### Interventions

In the IUI cycles, ovulation detection is performed with Luteinising Hormone (LH) tests or by transvaginal sonography, depending on the local setting. In case of monitoring with urinary LH tests, women test their urine once per day, starting on an individually calculated cycle day based on their basal body temperature chart. Women are inseminated with processed semen the day after the endogenous LH surge has been detected in the urine sample. Serum LH measurements are performed from day 11 of the menstrual cycle onwards and women are inseminated 1 day after the serum LH rise.^9^ In case follicular growth is monitored by transvaginal sonography, timing of insemination can be performed by ovulation triggering or by measuring serum LH levels. In case of ovulation triggering human chorionic gonadotropin (Pregnyl, Organon, Oss, The Netherlands) is administered when the dominant follicle has a diameter of at least 16 mm. Women are inseminated 36 to 40 hours thereafter. The semen may be processed in two ways. One way is to process the semen against a density gradient centrifugation and/or a washing step with culture medium according to local laboratory protocol after thawing of the—unprocessed—cryopreserved semen and the second way is to process the semen against a density gradient centrifugation and/or washing step with culture medium according to local laboratory protocol before freezing of the semen. In the ICI cycles, ovulation detection is in the same way as in the IUI arm and insemination is also timed identical to the IUI arm. Women are inseminated with unprocessed semen once per cycle, and preferably by a cervical cap.^6^ Before starting a new treatment cycle with IUI or ICI, women undergo a pregnancy test (Human gonadotrophin hormone (hCG) measurement in serum or urine). If the woman is not pregnant the next treatment cycle is started according to protocol. In case of a positive pregnancy test, women are monitored by transvaginal sonography. Monitoring will take place at 5 to 9 weeks of amenorrhoea to check whether an intrauterine gestational sac is present, that is, a clinical pregnancy.

Subsequently, monitoring takes place at 11 to 12 weeks amenorrhoea to register the presence of an intrauterine gestational sac with fetal heartbeat, that is, an ongoing pregnancy.

#### Follow up

Pregnant women undergo an ultrasound at 7 and 11 weeks of gestation to classify the pregnancy as clinical or ongoing singleton or multiple pregnancy. Women are contacted by telephone to enquire on the course of pregnancy, delivery and the health of the child. Detailed information on maternal complications will be obtained from the responsible obstetrician or midwife. When data on the health of the child are insufficient, child health centres and/or paediatricians are contacted for specific information. Presumably, not all women complete the 8 months of treatment. Couples who drop-out will largely represent normal patient flow. In both arms, women will be treated until ongoing pregnancy occurs within a time horizon of 8 months. We aim to keep track of all couples who drop-out and to document the reason for the drop-out.

#### Patient and public involvement

The Dutch patient organisation for patients with fertility problems (Freya) supports the study. When the study is finished, we will request Freya to organise an informal meeting during which fertility experts from our study group will present information on the treatment options. We will ask Freya to publish an easy to read summary of the results on their homepage. The data will thus become available for the public. Study participants are asked if they want to be informed about the results of the study during the informed consent procedure.

#### Primary outcome measure

The primary outcome is ongoing pregnancy leading to live birth. Ongoing pregnancy is defined as a positive heartbeat at 12 weeks of gestation. Only ongoing pregnancies that occur within the first eight months after randomisation count for assessment of the primary endpoint.

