#### Power calculation

The study is designed as a non-inferiority trial. We assume that six cycles can be completed within a fixed time horizon of 8 months. Assuming a live birth rate of 40% after six cycles of IUI, we need 208 women per arm with an alpha of 0.05, and a beta of 0.80 to demonstrate the non-inferiority of ICI with a margin of 12%.^7^

The margin of 12% are the differences shown in literature between IUI and ICI.^3^

A limitation of our study is that we use a non-inferiority margin of 12%. Most clinicians and patients would feel that 12% is a rather large and clinically relevant difference.

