#### Data analysis

We will compare baseline measurements female age, body mass index, indication for AID, previous assisted reproductive treatments, previous pregnancies, parity, intoxication and referral status.

The analysis of all outcomes is on an intention-to-treat basis. For ongoing pregnancy we will test non-inferiority on basis of the absolute risk difference with the absolute margin of 12%. We will subsequently estimate differences in the primary and secondary outcomes as relative risks with 95% CI. We will also report p values.

We will evaluate association and interaction with our primary outcome of baseline variables in logistic regression analyses. The baseline variables that we plan to include in these analyses are timing, sperm quality and practice variation.

We will construct Kaplan-Meier survival curves for time to ongoing pregnancy.

For continuous variables, we examine the distribution of the observations, and if normally distributed, we summarise them as means with SDs. If they are not normally distributed, medians and IQRs are reported. For dichotomous data, we provide proportions (or percentages). In addition to the baseline and outcome data, we also summarise the recruitment numbers, those lost to follow-up, protocol violations and other relevant data. We will analyse a maximum of six cycles of IUI or ICI performed within a time horizon of eight months after randomisation.

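### The 8-month window of the primary endpoint is tied to conception in the Abstract but, read literally, to the 12-week heartbeat in the Methods, and the tested endpoint drifts between live birth and ongoing pregnancy

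*Protocol article*

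**What the plan says.** All references are to the protocol article.

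**The window**

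- Abstract, Methods and analysis: "The primary outcome is ongoing pregnancy leading to live birth conceived within eight months after randomisation".
- Primary outcome measure: "Ongoing pregnancy is defined as a positive heartbeat at 12 weeks of gestation", followed at once by "Only ongoing pregnancies that occur within the first eight months after randomisation count for assessment of the primary endpoint".
- Objective: six cycles of each method are compared "within a time horizon of eight months".
- Power calculation takes it that six cycles fit into 8 months. The last sentence of Data analysis includes up to six cycles carried out in that period.

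**The endpoint**

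- Primary outcome measure: "The primary outcome is ongoing pregnancy leading to live birth". The Abstract also requires live birth.
- Power calculation: "Assuming a live birth rate of 40% after six cycles of IUI". The sentence cites the same reference as the cohort study in the Introduction, whose result is given there as "Cumulative ongoing pregnancy rates over six treatment cycles were 40.5% for IUI and 37.9% for ICI".
- Data analysis: "For ongoing pregnancy we will test non-inferiority on basis of the absolute risk difference with the absolute margin of 12" per cent.
- Data safety monitoring board: the interim look is described as being on the primary endpoint, but it rests on ongoing pregnancy after at least 3 months of follow-up.

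**The confirming scan**

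- Interventions puts it at 11 to 12 weeks of amenorrhoea and Follow up at 11 weeks. The definition in Primary outcome measure uses 12 weeks.

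**The concern.** A heartbeat at 12 weeks of gestation is seen about 10 weeks after insemination. If that event must fall inside the 8 months, the last 10 weeks of the treatment period can yield no success, yet cycles performed then are still part of the planned comparison. If only conception must fall inside the 8 months, all those cycles count. The two wordings therefore give different numerators for the same women.

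In a non-inferiority trial the direction matters. Cutting off late cycles lowers both cumulative rates and brings them closer together, while the margin stays at 12 absolute points. A shortfall of ICI over the full six cycles is then harder to detect.

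The label also moves. If the confirmatory test is on ongoing pregnancy, a loss after 12 weeks still counts as a success. If it is on live birth, it does not. The test sentence does not say which applies.

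**Working it through.** **Inputs from the article:** 8-month horizon; heartbeat at 12 weeks; 40% with IUI over six cycles; margin 12 points; alpha 0.05; power 80% (printed as a beta of 0.80); 208 per arm.

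**Assumptions, not in the article:** cycle 1 starts on the day of randomisation; insemination on cycle day 14; cycles of equal length L; no drop-out; constant per-cycle chance; 12 weeks counted from the first day of the cycle (84 days, so 70 days after insemination).

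**1. The plan's own sample size.** With 40% in both arms and one-sided alpha 0.05:

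n = (1.645 + 0.842)² × 2 × 0.40 × 0.60 / 0.12² ≈ 206.1, so 207 per arm, against 208 stated. The figure reproduces.

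**2. The two cut-offs.** 8 months = 8 × 365.25/12 = 243.5 days.

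- Window tied to conception: insemination up to day 243.5 counts.
- Window tied to the 12-week heartbeat: the cycle must start by day 243.5 − 84 = 159.5, with insemination by day 243.5 − 70 = 173.5 (5.7 months).

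**3. Which cycles can still count under the literal reading.** Cycle 6 reaches 12 weeks on day 5L + 84.

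| Pace | Cycle 6 reaches 12 weeks | Cycles that count |
|---|---|---|
| L = 28, back to back | day 224 | 6 |
| L = 30, back to back | day 234 | 6 |
| L = 31, back to back | day 239 | 6 |
| L = 32, back to back | day 244 | 5 |
| L = 28, 28 days lost to a late start or skipped cycle | day 252 | 5 |
| L = 28, 56 days lost | day 280 | 4 |
| six cycles spread over 8 months (L = 40.6) | day 287 | 4 |

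The slack before cycle 6 is lost is 159.5 − 5L: 19.5 days for L = 28, 9.5 for L = 30, 4.5 for L = 31. In every row all six inseminations fall before day 243.5, so all six count if the window is tied to conception.

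**4. Effect on the rate.** Per-cycle chance p = 1 − 0.60^(1/6) = 0.0816.

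- Six cycles: 40.0%.
- Five cycles: 1 − (1 − p)⁵ = 34.7%, a loss of 1 − 34.7/40.0 = 13%.
- Four cycles: 1 − (1 − p)⁴ = 28.9%, a loss of 1 − 28.9/40.0 = 28%.

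**5. Effect on power.** With equal arms and the 12-point margin, the formula in step 1 needs 207, 195 and 177 per arm for six, five and four cycles. Power with 208 per arm is 80.3%, 82.3% and 85.4%. The sample size is not harmed.

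**6. Effect on the conclusion.** Let ICI be exactly at the margin over six cycles: 40% v 28%. The ICI per-cycle chance is 1 − 0.72^(1/6) = 0.0533.

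| Cycles that count | IUI | ICI | True difference | Chance of declaring non-inferiority (one-sided 0.05) |
|---|---|---|---|---|
| 6 | 40.0% | 28.0% | 12.0 points | 5% |
| 5 | 34.7% | 23.9% | 10.7 points | 8.7% |
| 4 | 28.9% | 19.7% | 9.2 points | 16.5% |

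The last column is Φ[(0.12 − d)/SE − 1.645], with d the true difference and SE = √[(p₁(1 − p₁) + p₂(1 − p₂))/208]. For five cycles: (0.12 − 0.107)/0.0443 ≈ 0.29, and Φ(0.29 − 1.645) ≈ 8.7%. For four: (0.12 − 0.092)/0.0418 ≈ 0.67, and Φ(0.67 − 1.645) ≈ 16.5%. At one-sided 0.025 the chances are 2.5%, 4.7% and 9.9%.

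**7. The endpoint label.** No arithmetic applies. Abstract and Primary outcome measure require live birth, and Power calculation assumes a live birth rate of 40%, apparently taken from an ongoing pregnancy rate of 40.5%. The non-inferiority sentence in Data analysis and the interim look name ongoing pregnancy. Live birth cannot be known after 3 months of follow-up, so the interim look cannot be on the endpoint as defined.

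**The case against.** The strongest reply is that *occur* is loose wording for *are conceived*. The Abstract says so, and the last sentence of Data analysis, which includes cycles performed within the 8 months, fits that reading. This is probably what was meant. But the rule stands in the section that defines the endpoint, directly after the sentence that fixes ongoing pregnancy at 12 weeks, so it still has to be corrected.

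The second reply is that the trial enrols women with regular cycles, and back-to-back cycles of up to 31 days lose nothing. That is correct. A reader might infer that the rule certainly discards the last cycles, or that the trial in effect compares only four or five. The article gives no pace of cycles, so it does not support that. It is equally true that one skipped 28-day cycle is enough to lose cycle 6.

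Third, *ongoing pregnancy* in Data analysis may be shorthand for the full outcome, since the next sentence speaks of the primary outcome. That is possible for the test. It cannot hold for the interim look.

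Three further inferences should not be drawn:

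- That a lower rate undercuts the basis of the margin. Power calculation takes the 12% from differences in the literature, not from the 40%.
- That the Abstract and Methods disagree on live birth. They agree; the mismatch lies with the power, analysis and interim text.
- That the numerator could be chosen after seeing the data. The full protocol and any SAP are not shown and may settle it.

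**Conclusion.** The point holds as a contradiction on the literal text and at the least an ambiguity in the primary endpoint. The two windows differ by about 70 days. Under the literal Methods rule the loss ranges from none to about 28% of pregnancies (40% falling to 34.7% or 28.9%), depending on cycle pace. These figures assume a constant per-cycle chance, insemination on day 14 and no drop-out.

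The 208 per arm is unaffected. What changes is the meaning of the test: with five or four countable cycles, a true 12-point deficit appears as about 10.7 or 9.2 points, and the fixed margin grows from 30% of the control rate (0.12/0.40) to 35% or 42%. Both shifts make a non-inferiority conclusion easier to reach.

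The drift between live birth and ongoing pregnancy is a separate inconsistency. The article gives no rate of loss after 12 weeks, so its size cannot be stated.

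**What to change.** - In Primary outcome measure, replace *occur* by *are conceived*, which matches the Abstract and the last sentence of Data analysis. Add that the 12-week heartbeat and the birth count even when they fall after month 8.
- Use this one endpoint, with the live birth condition written out, in Primary outcome measure, in Power calculation and in the non-inferiority sentence of Data analysis.
- In Power calculation, say that the cohort figure in the Introduction is an ongoing pregnancy rate, if that is the source of the 40%.
- In the Data safety monitoring board section, state that the interim look uses ongoing pregnancy and not the full primary endpoint.
- Reconcile the scan timing in Interventions (11 to 12 weeks) and Follow up (11 weeks) with the 12-week definition.

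The cost is wording only. Follow up already tracks pregnant women to delivery and the health of the child, so the window change adds no visits, and the sample size stays as it is.

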#### Secondary outcome measures

Secondary outcomes are clinical pregnancy (any registered heartbeat at ultrasound), miscarriage (registered heartbeat before 12 weeks of gestation) and multiple pregnancy (registered heartbeat of at least two fetuses at 12 weeks of gestation) and ectopic pregnancy, time to ongoing pregnancy leading to live birth.

We will register the following pregnancy outcomes: preterm birth <37 weeks, iatrogenic preterm birth, spontaneous preterm birth, time to delivery, mean birth weight, birth weight <2.5 g, growth restriction defined as birth weight <10th percentile, pregnancy-induced hypertension, pre-eclampsia, HELLP syndrome, and direct and indirect costs.

#### Power calculation

The study is designed as a non-inferiority trial. We assume that six cycles can be completed within a fixed time horizon of 8 months. Assuming a live birth rate of 40% after six cycles of IUI, we need 208 women per arm with an alpha of 0.05, and a beta of 0.80 to demonstrate the non-inferiority of ICI with a margin of 12%.^7^

The margin of 12% are the differences shown in literature between IUI and ICI.^3^

A limitation of our study is that we use a non-inferiority margin of 12%. Most clinicians and patients would feel that 12% is a rather large and clinically relevant difference.

